#### Parent Measures

The CM-EA coach will track parent session attendance. All parent-reported measures will be collected at the 6-month follow-up. At that time, parents will complete a demographic interview similar to the one completed by the emerging adults as well as a parent version of the CSQ-8 [82] and the 3 implementation measures [81]. Finally, parents will also be engaged in a qualitative interview delving further into the acceptability, appropriateness, and feasibility of *Launch* services and the research protocol; the impact of CM-EA coaching and PRSS on parents and their emerging adult children; and any impacts on the parent-child relationship.

#### Recruitment and Retention Measures

The research team will track all potential participant research contacts of those interested in participating in the pilot project and will track all assessment completion statuses.

#### Peer Worker and Parent CM-EA Coach Measures

Peer workers delivering PRSS and the parent CM-EA coach will complete checklists of services delivered after each session and will engage in a follow-up qualitative interview at the end of their participation in the project. The peer workers will complete a checklist after each session to indicate which topics they covered with their emerging adult client. The CM-EA parent coach will complete a checklist after each session with each parent noting each CM-EA skill that the parent indicated using since the last time they met with the coach. Qualitative interviews with both types of participants will delve deeper into implementation-related concepts, perceived or actual impacts on emerging adults or parents, and other suggestions for service improvement.

#### Payers and Providers

Finally, payer and provider participants will engage in qualitative individual interviews throughout the study. Payers and providers will be asked about what kinds of participant-level outcomes or economic-related information they would want to know about as the result of a future large-scale study. They will also be asked to help inform the selection of appropriate comparators for the cost-effectiveness analysis as well as the selection of willingness-to-pay thresholds. Analysis procedures for all qualitative data are described in the following subsection.

### Analysis Plan

#### Aim 1

Aim 1 includes 2 groups of analyses. The first group is a preliminary psychometric evaluation of the adapted instruments measuring the adherence of (1) coaches training parents in the use of CM-EA and (2) standard PRSS plus vocational or educational skill building. The number of families is modest, but each will have numerous repeated measurements. The second group of analyses will determine whether coaches can train parents to deliver CM-EA and whether peer workers can deliver the combined services (ie, PRSS plus vocational or educational skill building). All data will be nested, with repeated measurements (level 1) nested within families (level 2), but the actual number of measurements will vary for each family and type of adherence. Nesting will be addressed using mixed-effects regression models. To evaluate parent training, the model will include a linear time term, which will estimate the initial level of coach adherence and test for change over time, and this will be interpreted relative to theory-based standards for acceptable training. To evaluate the delivery of PRSS plus vocational or educational skill building services, the same type of model will be performed. Combined, the results will determine whether the proposed protocols lead to the expected levels of adherence for coaches as well as peer workers, and low adherence scores will be investigated during the proposed qualitative interviews.

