Additional participant categories that will not be recipients of an intervention but who will directly inform the feasibility- and acceptability-related outcomes of the study include peer workers delivering *Launch* PRSS to emerging adult participants and a virtual CM-EA parent coach supporting parents. Payers and providers will also give feedback on the feasibility and acceptability of *Launch* and will inform the selection of key outcomes of interest (including cost-related outcomes) for the future large-scale study of *Launch*. For this study, payers and providers are defined as people working for organizations that may be responsible for funding services such as *Launch* whether via insurance or through grants (payers), individuals involved in the direct provision of services that could include services such as *Launch* (providers), or those involved in the administration or supervision of either payers or providers. We will use a multistage I (ie, funnel approach) purposeful sampling strategy [74] to ensure variation in payer or provider types while also targeting those with expertise on services for emerging adults with SU.

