### Protocol

#### Aim 1: Adaptation of Training Protocols

##### Overview

Members of our team have trained various providers (clinicians, probation officers, and students) in different versions of CM (including CM-EA) and other SU services over the past 15 years. As a result, we have established multifaceted training protocols to train and support diverse providers to deliver SU services with high adherence. To ensure that the materials fit the scope of the current project, we will adapt our training protocols to allow for virtual training and support of *Launch* for both the parent coach and peer workers.

A parent coach will train the parents to deliver CM-EA. However, for training the parent coach, a web-based CM-EA training support system will be used [77]. Developed by coinvestigator [name] with support from principal investigator [name] and modified from previous web-based CM training systems, it includes modules corresponding to each CM-EA component. Within each module, sections describe CM steps, give troubleshooting tips, and provide sample scripts and video examples. Each module can be completed in 1 to 2 web-based sessions depending on the activities involved (eg, some sessions include homework), and it takes the average user <8 hours to complete all modules. The website’s navigation guides users through the modules, and a passing score of 80% is required on a multiple-choice test to access the next module. Trainees failing to pass a test are able to rereview the module or access support from a CM-EA expert and can take the posttests to achieve a passing score. Furthermore, the team will adapt written training materials and develop a 3-day virtual CM-EA training for the parent coach, which will include *Launch* services review, role-playing, and other active training exercises that the team has successfully used across numerous research studies involving CM.

Similar web-based training protocols will be adapted with input from individuals with lived experience with SU recovery for peer workers to deliver the in-person emerging adult PRSS components. These are more straightforward because peer workers will already be trained and certified.

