## Results

We are currently engaging recovery community organizations as potential recruitment sites for emerging adult and parent participants, as well as for participating peer workers to take the vocational or educational toolkit training and deliver *Launch* services. We have also engaged a parent coach and initiated training. This project was funded (grant R34DA057639) in August 2023 and is currently expected to end in September 2025. We anticipate publication of the results of this study in late 2026. Participants are expected to begin enrolling in June 2024.

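### The Aim 1 adherence models have no provider level: the PRSS adherence level is stated too precisely if peer workers serve several families, and one coach cannot support a conclusion about coaches in general

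*Protocol article*

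**What the plan says.** The Analysis Plan for Aim 1 fixes the data structure: "All data will be nested, with repeated measurements (level 1) nested within families (level 2", with mixed-effects regression as the way to handle that nesting. For parent training, the model has a linear time term, "which will estimate the initial level of coach adherence and test for change over time", and the result is read against theory-based standards. For the peer workers: "To evaluate the delivery of PRSS plus vocational or educational skill building services, the same type of model will be performed". The analyses "will determine whether coaches can train parents to deliver CM-EA and whether peer workers can deliver the combined services", and "the results will determine whether the proposed protocols lead to the expected levels of adherence for coaches as well as peer workers".

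On the number of coaches, the article is mixed:

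- **Singular.** Participants lists "a virtual CM-EA parent coach supporting parents"; the Overview of Aim 1 (Adaptation of Training Protocols) says "A parent coach will train the parents to deliver CM-EA"; Results says "We have also engaged a parent coach and initiated training". The Aim 2 procedures and the section on peer worker and coach measures also refer to one coach.
- **Plural, with no number.** The Abstract (Methods), Adaptation of Adherence Instruments, and the Aim 1 analysis plan itself.

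The number of peer workers and their caseloads are not given. Ethical Considerations offers peer workers an optional monthly stipend for each emerging adult served. That allows several clients per worker but does not establish it.

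Sample Size and Power Considerations calls 48 families enough for accurate fixed effects. Its remark on nesting effects concerns power for the later trial, not the standard errors of this analysis.

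**The concern.** The family level accounts for repeated sessions within one family. It does not account for two families seeing the same provider, and here the outcome is what the provider does. A worker who follows the protocol closely will tend to do so with every client, so families that share a worker are not independent replicates of worker adherence. The two-level model counts them as if they were.

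The quantity at stake is the initial adherence level, because that is what is set against the standard. If its interval is too narrow, the PRSS training may be declared adequate or inadequate on less evidence than the output suggests. The variance between workers is also absorbed into the variance between families, so the pilot gives the later trial no information on clustering by worker.

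The coach raises a different problem. If there is one coach, every CM-EA family is a measurement on the same person. The between-coach variance cannot be estimated, yet the stated conclusion concerns coaches as a class.

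**Working it through.** **The plan's own figure.** The 48 families come from pilot guidance, not a power formula, so there is nothing to re-derive. The quoted rule of at least 12 per group is met: 48 / 3 = 16 per arm. This assumes equal allocation, because the ratio is not stated.

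**Families per adherence model.** Each component is delivered in two of the three arms: 2 × 16 = 32 families.

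**Assumed inputs.** Families per peer worker m = 4 to 8 (that is, 8 to 4 workers), and provider share of the between-family variance in adherence ρ = 0.1 to 0.3. Neither is in the documents.

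**Formulas for the adherence level.**

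- Design effect: DEFF = 1 + (m − 1)ρ
- Correct SE / reported SE = √DEFF
- Effective families = 32 / DEFF
- Real coverage of a nominal 95% interval = 2Φ(1.96 / √DEFF) − 1

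| m | ρ | DEFF | SE ratio | Effective families | Coverage |
|---|---|---|---|---|---|
| 1 | any | 1.0 | 1.00 | 32 | 95% |
| 4 | 0.1 | 1.3 | 1.14 | 24.6 | 91% |
| 4 | 0.2 | 1.6 | 1.26 | 20.0 | 88% |
| 4 | 0.3 | 1.9 | 1.38 | 16.8 | 85% |
| 8 | 0.1 | 1.7 | 1.30 | 18.8 | 87% |
| 8 | 0.2 | 2.4 | 1.55 | 13.3 | 79% |
| 8 | 0.3 | 3.1 | 1.76 | 10.3 | 73% |

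At the extremes, the reported SE is too small by 1 − 1/1.14 = 12% and 1 − 1/1.76 = 43%.

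**Simulation check.** 4,000 runs used 32 families with 20 sessions each (an assumed number) and a provider share of the initial-level variance near 0.2. A line was fitted per family and the coefficients averaged, which for balanced data is equivalent to the family-only mixed model.

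- *Initial level:* true SE / reported SE was 1.01 with 32 workers, 1.27 with 8 and 1.58 with 4; coverage was 95%, 89% and 79%. This agrees with the formula.
- *Time slope, workers differing in level only:* the ratio was 0.99 with 8 workers and 1.02 with 4, so there is no error.
- *Time slope, workers also differing in slope:* 1.16 with 8 workers and 1.36 with 4.

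**The coach.** With one coach, m = 32. For a statement about coaches in general, the formula would give DEFF = 1 + 31 × 0.1 = 4.1 (SE ratio 2.02) up to 1 + 31 × 0.3 = 10.3 (SE ratio 3.21). This is only an illustration: ρ cannot be estimated from one coach, so no model fitted to these data can supply the missing variance. For a statement about that one coach, the family-level SE needs no correction.

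**The case against.** The strongest reply is that this is a pilot with objectives rather than formal hypotheses, that its sample was not sized for testing, and that low adherence will be explored in interviews and watched in supervision. That limits the consequence to overstated precision on adherence; no efficacy claim is at risk. It does not remove the point, because the plan says its results will determine whether expected adherence is reached. Nor is this a detail left to a fuller document, since the two-level structure is stated.

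Three stronger readings are tempting and are not supported:

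- A reader might infer that the test of change over time runs at an inflated error rate of about 9% to 27% (the complement of 91% to 73% coverage). The design effect applies to the level, not to a within-family slope. The slope is the only test the Aim 1 plan names, and its SE is distorted only if workers differ in slope, for which the documents give no evidence.
- A reader might infer that the coach model's standard errors are wrong. With one coach, no coach level can be fitted and the family-level SE is valid for that coach. What is too broad is the conclusion.
- A reader might take shared peer workers as a fact, or as the main source of dependence. The documents do not give caseloads, and recovery organizations were still being engaged.

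The plural wording in several places also means that a single coach is the better reading, not a certainty.

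**Conclusion.** The point holds in two limited parts.

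**PRSS.** Whenever peer workers serve more than one family and differ in adherence, the initial level is reported too precisely. Over the assumed range the reported SE is 12% to 43% too small. The size rests on equal allocation, caseload and provider variance share, none of which the article states. It is zero at one family per worker or with no variance between workers.

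**CM-EA.** If there is one coach, the analysis can show whether that coach reached the expected adherence, which is a useful pilot result. It cannot show whether coaches in general do. This part needs no assumed variance share, only the number of coaches, which the article should make consistent.

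**What to change.** - **PRSS adherence models:** add peer worker, as a random intercept with small-sample degrees of freedom, or as fixed effects if workers are few. Report the number of workers and the families per worker.
- **CM-EA adherence model:** reconcile the singular and plural wording. If there is one coach, state that estimates are conditional on that coach and limit the Aim 1 conclusion to the study coach.
- **Optional sensitivity analysis:** add the order in which families started as a covariate, to help separate the coach's learning across successive families from change within a family. Adherence ratings feed back through supervision and booster training, so such learning is plausible.

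The change is to analysis wording. It needs provider identity and start dates in the data set; session checklists and attendance tracking are already planned, but the article does not list these fields, so this should be confirmed. The costs are wider intervals, a worker variance that will itself be imprecise when workers are few, and a narrower claim about coaching.

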#### Aim 2: Feasibility of Launch Recruitment, Assessment, and Retention

##### Overview

The feasibility of recruitment will be evaluated by comparing the proportion of families recruited to the target rate of 75%, as well as comparison to demographics of families who decline participation after completing screening (eg, emerging adult biological sex, race, and ethnicity). The feasibility of the assessment design and retention of parents and their emerging adult children will be evaluated using a 2-level multivariate and repeated measures model, with completion status at repeated assessment occasions (level 1; two assessments per family) nested within families (level 2; 48 families). The model estimates the overall log-odds of assessment completion, and subsequent models will test for differences by condition (parent CM-EA only vs standard PRSS plus vocational or educational skill building vs combined services), demographics (eg, emerging adult biological sex), and emerging adult poly-SU profile.

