## Methods

### Overview

This pilot study will assess the feasibility and acceptability of *Launch,* an innovative service package for poly-SU in emerging adults that can be scaled up for rural communities. Consistent with the appropriateness of a pilot study, this study will examine objectives rather than formal hypotheses. In particular, this study will accomplish the following activities: (1) adapting and developing peer worker training protocols and adherence tools, (2) gathering pilot data on a small sample of the population to test the acceptability and feasibility of *Launch*, and (3) gathering information from payers and providers in preparation for a larger effectiveness trial of *Launch*. This study uses a mixed methods and multi-informant assessment design involving collection of both qualitative and quantitative data [72]. A total of 48 emerging adults with poly-SU problems and their parents will be primarily recruited from sites that provide services to clients living in rural areas. The emerging adults will be randomized to one of three conditions: (1) virtual parent CM-EA coach for parents only, (2) in-person PRSS plus vocational or educational skill building for emerging adults only, or (3) a combination of virtual parent CM-EA coaching for parents *and* in-person PRSS plus vocational or educational skill building for emerging adults. Payers and providers of recovery services will be recruited for qualitative interviews.

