After recruitment, interested participants will meet with a research team member to complete informed consent. Then, emerging adults will complete an approximately 1-hour virtual baseline interview. On the basis of the experience of the research team, 1-hour assessments rarely present a significant response burden, but the research team will use breaks to attenuate circumstances that threaten the validity of the assessments. A stratified permuted block randomization design [80] will be used to randomize the families to one of three treatment conditions: (1) web-based CM-EA parent coaching only, (2) in-person PRSS for the emerging adult only, or (3) both web-based CM-EA parent coaching and in-person PRSS for the emerging adult. Families will receive *Launch* services for approximately 5 months. All activities with the parents will be web-based, assessments with emerging adults will be web-based, and PRSS sessions with the emerging adults will be in person. The parent coach and peer workers will track session attendance. At 6 months after the baseline, emerging adults will complete a virtual, 1-hour follow-up assessment, and parents will complete an approximately 1-hour qualitative interview (see the *Measures* section) that will also include a limited number of brief quantitative questionnaires. At the end of their participation in the project, the parent coach and peer workers will complete an approximately 1-hour qualitative interview about *Launch* services (see the *Measures* section).

#### Aim 3

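### On its natural reading, the retention model pools a baseline that is complete by design with the 6-month visit, which overstates retention and leaves parents out

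*Protocol article*

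**What the plan says.** The Analysis Plan, Aim 2 (feasibility of recruitment, assessment and retention, Overview) states that "retention of parents and their emerging adult children will be evaluated using a 2-level multivariate and repeated measures model". The data for that model are "completion status at repeated assessment occasions (level 1; two assessments per family) nested within families (level 2; 48 families"). On the estimand and the comparisons it says: "The model estimates the overall log-odds of assessment completion, and subsequent models will test for differences by condition", and also by demographics and polysubstance profile.

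Three other places bear on this:

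- **Protocol, Aim 2** gives the order of steps. Consent comes first. "Then, emerging adults will complete an approximately 1-hour virtual baseline interview". Randomisation to the three conditions is described after that, and the follow-up assessment is at 6 months.
- **Parent Measures**: "All parent-reported measures will be collected at the 6-month follow-up".
- **Ethical Considerations** pays the emerging adult for two assessments (baseline and 6 months) and the parent for one (6 months).

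The section sets no retention target. Its 75% figure is for recruitment.

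**The concern.** Retention is whether a randomised participant is still providing data at the end. If one of the two records per family is a visit that had to happen before the family could be randomised, that record says nothing about retention. Averaging it with the 6-month record pulls the estimate towards 100%.

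The count of two also does not fit the schedule. A family has three assessments, and the parent has only one of them, so the parent contributes no repeated measure.

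The figure matters because Sample Size and Power Considerations says the pilot will inform sample size planning for the larger trial. An attrition allowance taken from the pooled rate would be half the true loss.

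**Working it through.** **Inputs**

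- 48 families with two records each, so 96 records (Analysis Plan, Aim 2).
- Two occasions, baseline and 6 months; baseline precedes randomisation (Protocol, Aim 2).
- Parents assessed at 6 months only (Parent Measures).
- The 6-month completion rate r is not given anywhere, so it is an assumption and is shown over a range. There is no retention figure in the article to reproduce.

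**Step 1: what the overall rate estimates.** With baseline complete for all 48 families and k families complete at 6 months, r = k/48, and

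pooled rate = (48 + k)/96 = (1 + r)/2

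overstatement = (1 + r)/2 − r = (1 − r)/2

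ratio of pooled odds to true odds = (1 + r)/r

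| 6-month completion (assumed) | True rate | Pooled rate | Overstatement (points) | True log-odds | Pooled log-odds | Odds ratio, pooled to true |
|---|---|---|---|---|---|---|
| 24/48 | 50.0% | 75.0% | 25.0 | 0.00 | 1.10 | 3.00 |
| 29/48 | 60.4% | 80.2% | 19.8 | 0.42 | 1.40 | 2.66 |
| 34/48 | 70.8% | 85.4% | 14.6 | 0.89 | 1.77 | 2.41 |
| 36/48 | 75.0% | 87.5% | 12.5 | 1.10 | 1.95 | 2.33 |
| 38/48 | 79.2% | 89.6% | 10.4 | 1.34 | 2.15 | 2.26 |
| 43/48 | 89.6% | 94.8% | 5.2 | 2.15 | 2.90 | 2.12 |

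At 36/48 the exact 95% interval is 60.4% to 86.4%. For 84/96, treated as independent records, it is 79.2% to 93.4%. The pooled rate cannot fall below 50% even if nobody returns.

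**Step 2: does the two-level structure change this?** A random-intercept logistic model was fitted by maximum likelihood with baseline fixed at complete and 29, 34, 38 or 43 of 48 families complete at 6 months. The random-intercept SD was estimated as 0 each time, and the fitted rates were 80.2%, 85.4%, 89.6% and 94.8%. These equal the simple pooled rates, so the nesting does not correct the overstatement.

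**Step 3: differences by condition.** For conditions with 6-month rates a and b, the pooled difference is (1 + b)/2 − (1 + a)/2 = (b − a)/2. For an assumed 60% against 85%, the pooled rates are 80% and 92.5%. The risk difference drops from 25 to 12.5 points and the odds ratio from 3.78 to 3.08.

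**Step 4: parents.** Scheduled assessments per family: emerging adult at baseline, emerging adult at 6 months, parent at 6 months, which makes three. If the two records are the emerging adult's, parent completion does not enter. With an assumed 80% of emerging adults and 50% of parents complete at 6 months, the model reports (100% + 80%)/2 = 90%. The 6-month average over both informants is (80% + 50%)/2 = 65%.

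**Step 5: effect on planning.** With r = 75%, the pooled rate implies an allowance for 12.5% loss when the true loss is 25%. A larger trial enrolled on that basis would finish with 0.75/0.875 = 86% of the completers it needs.

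**The case against.** The strongest reply is that the section never says which two assessments it means. They could be the emerging adult's and the parent's 6-month assessments. That would explain why the model is called multivariate and would cover both informants, with no inflation. It is a possible reading, but it does not fit the phrase about repeated occasions, because both records fall at one time point. It would also leave baseline out of a model that is meant to cover the assessment design as well. No reading of two covers the three scheduled assessments.

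A second reply is that no sentence makes a completed baseline a condition of randomisation; only the order of steps implies it. This stands as a caution. If a share b of randomised families completed baseline, the overstatement is (b − r)/2 instead of (1 − r)/2, so a small shortfall changes little.

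A third is that the full analysis plan may include a term for occasion or for informant. An occasion term would separate the 6-month rate from baseline. The text, however, names a single overall log-odds as what the model estimates.

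A reader might also infer several stronger points that the documents do not support:

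- **Poor retention would be declared acceptable.** No retention threshold is set, so no stated decision can flip. Completion statuses are tracked for all assessments, so the 6-month figures will exist.
- **Retention is half of aim 2.** Objectives lists it as one of four elements in the first of two parts.
- **A zero variance component does harm.** It only reduces the model to ordinary logistic regression.
- **Late collection of parent demographics breaks the analysis.** The predictors the article names are condition, demographics (its example is the emerging adult's sex) and the emerging adult's polysubstance profile. It does not announce an analysis of attrition by parent characteristics.
- **The comparisons by condition are an underpowered confirmatory test.** The Methods Overview says "this study will examine objectives rather than formal hypotheses", and the sample size section says the number was not set by power.

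**Conclusion.** The point holds on the natural reading, in which the two occasions are baseline and 6 months. The overall completion rate then estimates (1 + r)/2, overstates 6-month completion by (1 − r)/2, halves risk differences between conditions, and omits parents although their retention is a stated purpose of the model. The size is 12.5 points if r is 75%, and 25 to 5 points for r from 50% to 90%.

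This rests on two inferences, the identity of the two assessments and completion of baseline by essentially all randomised families, and on assumed values of r. The mismatch between two assessments in the model and three in the schedule depends on neither. It is enough by itself to require that the text be corrected.

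**What to change.** Define retention as completion of the 6-month assessment among randomised families, with one binary outcome for the emerging adult and one for the parent. Report each overall (out of 48) and by arm (out of the number randomised to that arm), with exact 95% confidence intervals. If a model is kept, nest informant (emerging adult, parent) within family at 6 months, so that the two records per family are the two that carry information on retention. Report baseline completion separately, with consented families as the denominator, as a measure of assessment feasibility.

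The change is to analysis wording only; it needs no extra visit, form or participant. The price is a retention figure that looks less favourable and a wider interval around it.

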#### Sample Size and Power Considerations

Because this study is *developmental work*, the sample size (n=48 families) was driven by appropriateness for pilot study objectives rather than by statistical power computations for formal hypothesis testing [96,97]. Pilot studies play an important role in providing information for the planning and justification of future large-scale trials (eg, for feasibility of service protocols and refinement of recruitment and assessment strategies) [98]. The sample size conforms to guidelines for pilot studies (n≥12 per group) [99,100] and provides representativeness of a diversity of participant characteristics for examining feasibility, data collection procedures, and *Launch* service acceptability. However, this pilot will inform power analyses and sample size planning for a subsequent larger effectiveness trial. Because of this, it is important for the measurement and research design to support accurate estimates of the focal model parameters—thus, there are important considerations regarding the precision of estimated effects. For the measurement models proposed, the sample is sufficient for stable and precise estimates of family and item parameters and SEs. Specifically, sample sizes in the range of 16 to 36 are sufficient for 95% confidence that the estimated person or item calibrations are stable within –1 logit to +1 logit [101]. It is also worth noting that this estimate is conservative because repeated measurements of adherence will provide additional data for evaluating the psychometric performance of the proposed instruments. For the proposed mixed-effects regression models, the sample of 48 families is sufficient for accurate estimates of the focal model parameters, in particular fixed-effects estimates for between-group differences and change over time [102]. Although variance components could be prone to bias, this information is less important for planning the subsequent larger trial as the power estimates can straightforwardly penalize for a range of nesting effects.

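### The claim that 48 families give accurate between-group estimates does not hold for the model comparing assessment completion across the three conditions

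*Protocol article*

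**What the plan says.** Under Analysis Plan, Aim 2 (feasibility of recruitment, assessment and retention), the protocol article sets up a two-level model "with completion status at repeated assessment occasions (level 1; two assessments per family) nested within families (level 2; 48 families"). The outcome is therefore binary, and the article gives the scale of the fit: "The model estimates the overall log-odds of assessment completion". Once that overall fit is done, "subsequent models will test for differences by condition", with demographics and polysubstance use profile examined as well.

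Sample Size and Power Considerations says that the number of families was not derived from power. It checks the number against a rule of thumb: "The sample size conforms to guidelines for pilot studies (n≥12 per group"). It then turns to the precision of estimated effects and states, for the proposed mixed-effects models, that "the sample of 48 families is sufficient for accurate estimates of the focal model parameters, in particular fixed-effects estimates for between-group differences"; trends over time are named too. The only reservation is about variance components.

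Two other places bear on the point. Under Secondary Outcomes, the article says power is too low for any statistical analysis of those outcomes and plans descriptive statistics. The Methods overview says that "this study will examine objectives rather than formal hypotheses".

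**The concern.** The completion model is a two-level model with an explicit contrast between conditions, so the accuracy statement covers it. The outcome is binary, and each of three arms holds about a third of 48 families. That carries little information on an odds ratio, whatever the completion rate.

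Retention is an Aim 2 objective, and the pilot is meant to inform planning of a larger trial. If the between-condition estimates are described in advance as accurate, a non-significant comparison could be carried forward as evidence that retention is the same under parent coaching, peer support and both, when the data could not show a sizeable deficit. A planner might also take up an unstable odds ratio as if it were well estimated.

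**Working it through.** **Inputs from the article.** 48 families; three arms ("randomize the families to one of three treatment conditions"); two assessments per family; a log-odds model.

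**Assumptions.**
- Allocation is 1:1:1, since no ratio is stated.
- Completion p lies between 60% and 95%, since no expected rate is given. The 75% in the Aim 2 analysis is a recruitment target. The nearest retention figure is in the Introduction: up to 70% at 8 weeks, as background on contingency management.
- One occasion per family is informative. The Protocol section describes the emerging adult baseline interview before randomization. If the two assessments are baseline and 6 months, baseline is complete by design among randomized families and says nothing about differences between arms. The other reading is that both can be missed, since the emerging adult and the parent each have a 6-month assessment. I therefore also show a best case of 32 independent assessments per arm.

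**The plan's own figure.** 48/3 = 16, which meets the guideline of at least 12 per group. The accuracy statement has no standard error, interval width or power attached, so it cannot be reproduced.

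**Precision of a pairwise odds ratio.** With the same p in both arms, SE(log OR) = √(2/(n·p·(1−p))), and the 95% interval runs from OR/f to OR×f with f = exp(1.96·SE). For example, at p = 0.70 and n = 16: SE = √(2/3.36) = 0.77 and f = 4.5.

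| p | Expected non-completers, 48(1−p) | SE, n = 16 | f, n = 16 | f, n = 32 independent |
|---|---|---|---|---|
| 0.60 | 19.2 | 0.72 | 4.1 | 2.7 |
| 0.70 | 14.4 | 0.77 | 4.5 | 2.9 |
| 0.80 | 9.6 | 0.88 | 5.7 | 3.4 |
| 0.85 | 7.2 | 0.99 | 7.0 | 3.9 |
| 0.90 | 4.8 | 1.18 | 10 | 5.1 |
| 0.95 | 2.4 | 1.62 | 24 | 9.5 |

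To put f = 4.5 on the completion scale, hold one arm at 70% (odds 2.33) and suppose the estimated odds ratio is 1. The limits for the other arm are odds of 2.33/4.5 = 0.52 and 2.33×4.5 = 10.5, that is, completion of 34% to 91%. For a single arm, 14 of 16 completed has an exact 95% interval of 62% to 98%.

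**Power.** Two arms of 16, 20-point difference: 70% v 50%, 21%; 75% v 55%, 21%; 80% v 60%, 23%; 90% v 70%, 29%. For 80% v 60%, 82 per arm would be needed for 80% power. A simulated three-arm chi-square test with one low arm gives similar values: 90/90/70, 30%; 80/80/60, 23%; 70/70/50, 21%.

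**Chance that some arm has no non-completers.** For n missable assessments per arm this is 1 − (1 − pⁿ)³.

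| p | n = 16 | n = 32 independent |
|---|---|---|
| 0.70 | 1% | under 0.1% |
| 0.80 | 8% | 0.2% |
| 0.85 | 21% | 1.6% |
| 0.90 | 46% | 10% |
| 0.95 | 82% | 48% |

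Correlation within families would move the last column back towards the middle one.

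**The case against.** The best defence of the text is that accurate may mean unbiased, since the sentence is set against possible bias in variance components and rests on a cited source that is not at hand. Some of this stands, but the same paragraph introduces the subject as precision of estimated effects, and a reader will take it so. It is also fair that the sample was not powered for hypothesis tests and that the limitations section concedes the restrictions of a small sample. Neither withdraws the specific statement about between-group differences.

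Several stronger readings are tempting, and the document does not support them:

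- **That there will be only a handful of non-completers, so the models will fail.** No retention rate is planned. At 70% there would be about 14 non-completers and a 1% chance of an arm with none. Failure is a serious risk only at roughly 85-90% completion or above, and less so if both assessments can be missed.
- **That an empty cell makes the test meaningless.** It breaks the ordinary maximum likelihood estimate and its Wald test. Likelihood-ratio, score and exact tests remain usable.
- **That all predictors enter one overloaded model.** The article speaks of models in the plural, so condition, demographics and profile may be examined separately.
- **That testing contradicts the absence of formal hypotheses.** Exploring who fails to complete is a feasibility objective, so the tension is weak. Nor does the article fix the number of tests, so no false-positive rate can be put on them.

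The article also does not say that a null result will be read as equal retention, and no progression rule depends on it. The harm is a risk of misreading. Handling of sparse cells may be set out in a full analysis plan that is not shown.

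**Conclusion.** The point holds as a correction to the accuracy statement. For completion by condition, no rate from 60% to 95% gives an odds ratio that could be called accurate. The interval factor is 4.1 at best with 16 informative outcomes per arm, and 2.7 at best if 32 independent assessments per arm are credited. Power for a 20-point deficit in one arm is about 20-30%. These figures assume equal allocation and use a large-sample formula that is itself rough at high completion, where few non-completers are expected.

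Non-estimability is a secondary risk that depends on a high completion rate, which the article neither states nor rules out. The statement also sits awkwardly beside the decision to keep the secondary outcomes descriptive for want of power, since completion by arm is similarly short of information. This should be fixed, but it does not undermine the pilot's purpose or its sample size as such.

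**What to change.** In the Aim 2 analysis of assessment and retention:

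- Make the main retention result the completion proportion per arm and per subgroup with exact or Wilson 95% intervals, together with differences between arms and their intervals.
- Label any model-based comparison by condition, demographics or polysubstance use profile as exploratory, and use a penalised (Firth-type) fit where cells are sparse.
- State that a non-significant comparison will not be read as equal retention.

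In Sample Size and Power Considerations, restrict the accuracy claim so that it does not cover between-condition differences in completion.

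The cost is analysis wording and a less favourable precision statement. The sample size, data collection and conduct of the pilot do not change.
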